### *Secondary outcomes:*

#### Pregnancy and childbearing

- proportion of girls who have ever given birth after 2 years of programme implementation;
- proportion of girls who have ever been pregnant after 2 years of programme implementation;
- proportion of girls who have ever been pregnant before their 16^th^ birthday;
- proportion of girls who have ever given birth before their 16^th^ birthday;
- proportion of girls who have ever been pregnant before their 18^th^ birthday;
- socioeconomic equity in proportion of girls who have ever given birth before 18^th^ birthday;

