## Participant population

#### The participant population will be girls enrolled in grade 7 (average age approx. 14 years) in 2016 in rural basic schools in the twelve study districts.

## Eligibility criteria

All girls enrolled in grade 7 in the included schools will be eligible to participate, including those who are already married or have children. Girls without a parent or legal guardian living in the household will also be eligible to participate if the headmaster of their school or the headman of the village gives consent. There will be no age restriction.

Girls who drop out of school after they have been recruited will continue to be part of the trial.

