| **Parameter** | **Assumed level** | **Comment** |
| --- | --- | --- |
| Incidence of births before girls’ 18th birthday | 0.08 | We assume that 27% of girls in the control arm will have given birth before their 18th birthday. This corresponds to an average incidence rate of (27%-3%)=8% per year over the average 3 year period (from the time the average age is 15). |
| Effectiveness (i.e. (1-RR)×100 of economic intervention vs control | -25% | I.e. the incidence in economic intervention arm assumed to be 0.06 |
| Effectiveness of combined intervention vs control | -40% | i.e. the incidence in combined intervention arm assumed to be 0.048 |
| Effectiveness of combined intervention vs economic intervention | -20% | The combined intervention will offer [1-(0.0.048/0.06)], i.e. 20% more relative protection than the economic intervention alone. |
| Cluster size | 28 | Average number of girls in grade 7 in the selected schools is 31. If we assume that up to 10% may be lost to follow up by the time of measuring the outcome, the average cluster size will be 28 |
| Person years per cluster | 84 | If 28 participants are followed up for 3 years on average, person years per cluster are 84. |
| Coefficient of variation (k) | 0.15 | The ICC was 0.00737 for “ever pregnant” after intervention period in cash transfer trial in Malawi (estimate obtained from [name]). This corresponds to k=0.15 when the total proportion who have given birth by this time is 0.27 [51]. |
| Z_1_ (acceptable alpha error level) | 1.96 |  |
| Power for comparison of economic intervention vs combined intervention | 70% | We need 63 clusters in each of the intervention arms to have 70% power to detect the assumed difference |
| Power for comparison of economic intervention vs control | 80% | We need 39 clusters in each arm to have 80% power to detect the assumed difference. The PASS power calculator for incidence rates does not allow for unequal trial arms, but the PASS function for proportions indicates that 63 economic and 31 control will give slightly higher power^[[5]](#endnote-2)^ |
| Power for comparison of combined intervention vs control | >95% | We need 23 clusters in each arm to have 95% power to detect the assumed difference. |
|  |  |  |

*Assumptions for sample size required to measure the primary outcome ‘proportion of girls who sit for grade 9 exam’*

| **Parameter** | **Assumed level** | **Comment** |
| --- | --- | --- |

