## Recruitment

Research assistants will between March and June 2016, i.e. in terms 1 and 2, visit selected schools (with grade 7) and inform girls who are enrolled in grade 7 about the study. The parents/guardians of girls in grade 7 will be invited to an information meeting. If their daughter is < 18 years, they will be asked to give consent to her participation in the trial. A few days later the research assistants will return to the school and ask girls to consent (if they are ≥18 years) or assent (if they are younger than 18 years and their parents or legal guardians have consented) to participation. Those who consent/assent and participate in the baseline survey will be enrolled.

Repeat visits will be made to the school to give girls who are absent on the day of the visit a chance to be enrolled.

Addresses and mobile phone numbers of the girl (if any), parents/guardians and close relatives or neighbours will be recorded when consent/assent is obtained. The girl will be asked to specify the preferred telephone number that can be used to make phone-based follow-up contacts with her.

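### The two before-16 outcomes count girls whose status was settled before allocation, which dilutes the effect estimates

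*Protocol*

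**What the plan says.** Protocol, Secondary outcomes (Pregnancy and childbearing), lists "proportion of girls who have ever been pregnant before their 16^th^ birthday" and "proportion of girls who have ever given birth before their 16^th^ birthday". Neither entry limits which girls are counted.

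Under Eligibility criteria, "There will be no age restriction", and girls are eligible "including those who are already married or have children". Recruitment makes arrangements to "ask girls to consent (if they are ≥18 years) or assent", so older girls are expected at entry. Participant population describes "girls enrolled in grade 7 (average age approx. 14 years) in 2016" and gives no spread of ages.

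Statistical methods specifies intention to treat with all participants analysed in their allocated arm. The same section removes girls already married at the start from the analyses of marriage before 16 or 18. No matching rule is written for pregnancy or birth.

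The note on changes to the protocol records that birth measures moved from proportions to incidence rates in July 2016. It does not say whether birth before 16 was included, and it records no such change for pregnancy.

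**The concern.** Allocation is in July 2016 and the interventions start in September 2016. For a girl who is already 16 at allocation, the answer to both before-16 questions is fixed. The same is true of a younger girl who has already been pregnant (first outcome) or already given birth (second outcome), because an outcome worded as ever having had the event keeps earlier events.

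These girls stay in numerator and denominator in every arm and add only noise to the comparison. The absolute risk reduction and the number needed to prevent, both of which the protocol plans to report, would understate the effect in girls who could still benefit. The Background singles out pregnancy below 16 as especially hazardous, so a real effect there should not be blurred by the choice of denominator.

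**Working it through.** **Plan's own figure.** The before-16 outcomes have no stated rate, effect or power. The nearest sized outcome is birth within 8 months of the end of the intervention, combined versus control: rates 0.06 and 0.036 per year, 56 person-years per cluster, k = 0.20, 90% power. The cluster-rate formula gives 1 + (1.96 + 1.282)² × [(0.06 + 0.036)/56 + 0.2² × (0.06² + 0.036²)] / 0.024² = 35.8, so 36 clusters per arm, as stated. The sizing arithmetic is not in question.

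**Step 1: mean age at allocation.** Sample size puts the average age eight months after the intervention ends (about July 2019) at 17.1 years in two places and 17.5 in one. Three years earlier this is 14.1 or 14.5.

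**Step 2: share already 16.** With a normal age distribution, s = 1 − Φ((16 − mean)/SD). The SD is an assumption.

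| Mean at allocation | SD 0.75 | SD 1.0 | SD 1.5 | SD 1.8 |
|---|---|---|---|---|
| 14.1 | 1% | 3% | 10% | 15% |
| 14.5 | 2% | 7% | 16% | 20% |

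**Step 3: absolute scale.** Girls already 16 contribute no difference, so RD(all) = (1 − s) × RD(under 16). If a share b of girls under 16 already had the event, RD(under 16) = (1 − b) × RD(event-free). Both relations are exact, given balance between arms.

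**Step 4: relative scale.** RR(all) = [(1 − s)p₁ + s·h] / [(1 − s)p₀ + s·h], where p₀ and p₁ are the control and intervention risks in girls under 16 and h is the share of older girls who had the event before 16. Take p₀ = 8%, a true RR of 0.60 and s = 10%:
- h = 0: the RR stays 0.60.
- h = 11%: (0.9 × 0.048 + 0.011)/(0.9 × 0.08 + 0.011) = 0.0542/0.083 = 0.65.

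Earlier events at any age can matter as much. Suppose 3 of 11 percentage points precede allocation. The 11% is the census figure for having given birth at age 16 in three of the districts, and the 3% is the amount subtracted in the sizing tables; combining them is only an illustration. A true RR of 0.60 then appears as (3 + 8 × 0.60)/11 = 0.71.

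**Step 5: worked illustration.** Assume s = 10%, earlier events in 2% of girls under 16 and 10% of older girls, a control risk of 6% after allocation in event-free girls under 16, and a true RR of 0.60. Power is for 31 versus 63 clusters of 28 (smaller after restriction), ICC 0.00737, two-sided 5%.

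| Set analysed | Control | Intervention | RD (points) | RR | Power |
|---|---|---|---|---|---|
| All girls | 8.09% | 5.98% | 2.12 | 0.74 | 47% |
| Under 16 at allocation | 7.88% | 5.53% | 2.35 | 0.70 | 53% |
| Under 16 and event-free | 6.00% | 3.60% | 2.40 | 0.60 | 67% |

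For all girls versus girls under 16, power is 53% versus 56% at s = 3%, and 37% versus 49% at s = 20%. In this illustration, removing earlier events gains more than the age restriction alone.

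**The case against.** The outcome list gives labels, and the SAP, which is not at hand, may define the set at risk. Intention to treat does not settle it either, since the same section pairs it with the marriage exclusion. It also foresees handling left censoring where needed and a Cox model for time to first pregnancy, in which a girl already 16 would add nothing to a before-16 risk set. If the logged move to incidence rates covers birth before 16, girls past 16 add no person-time and their dilution of that outcome disappears. These points stand as reasons for modest weight. They do not remove the concern: the current list still says proportion, nothing addresses the pregnancy outcome, and the marriage rule shows that exclusions were written where they were intended.

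The all-girls proportion is also a legitimate quantity: the effect of offering the programme to a whole grade 7 class. That is a reason to keep it as supportive.

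A reader might go further in three ways that the documents do not support.
- **A large share already 16.** The sizing table counts three years "from the time the average age is 15". A mean of 15 at allocation would give 16% at SD 1.0 and 25% at SD 1.5. But that age opens a sizing window ending at 18 and is not dated to allocation.
- **That counting only events after allocation would not help.** It would help the risk ratio: older girls would then be non-events in both arms and the factor (1 − s) cancels. Only the absolute difference stays diluted.
- **That births need a firm cut-off at 15 years 3 months.** This assumes term deliveries and counts from the July allocation, although the programme starts in September.

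**Conclusion.** The point holds as one of dilution. As written, the two before-16 outcomes include girls whose status the programme cannot change. The loss on the absolute scale is certain and equals the share already 16. Its size is not known, because the protocol gives no age SD: about 3-15% at mean 14.1 and 7-20% at mean 14.5 for SD 1.0 to 1.8, and 1-2% at SD 0.75, all under an assumed normal distribution. On the relative scale the dilution depends on earlier events, in older and younger girls alike.

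A reader might infer bias between arms. The documents do not support that: randomisation should balance these girls, so the result is attenuation and lost precision, not a false effect. The outcomes are secondary and were not used for sizing, and in the illustration power is limited under every definition.

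**What to change.** In Secondary outcomes (Pregnancy and childbearing), define both before-16 outcomes among girls who are under 16 and without the event at allocation (never pregnant for the first, never given birth for the second), using baseline data. Alternatively, define them as incidence with person-time from allocation to the 16th birthday. Either follows the logic already applied to girls married at the start.

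Keep the all-girls proportion as a supportive analysis. State whether the logged change of birth measures to incidence rates covers birth before 16, and align the outcome list with it. Report the age distribution at allocation by arm. For births, a sensitivity analysis can be added in girls young enough at programme start to conceive afterwards and deliver before 16.

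The cost is a change of wording and somewhat fewer girls in two secondary analyses. The restriction uses only pre-allocation characteristics, so the randomised comparison is preserved.

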#### Marriage

- proportion of girls ever married/cohabiting before their 18^th^ birthday;
- socioeconomic equity in proportion of girls ever married/cohabiting before 18^th^ birthday;
- proportion of unmarried girls with boyfriend

#### School-related

- school attendance in grade 8 and grade 9;
- enrolment grade 8;
- school drop-out rate before grade 9 completed (will include both regular drop out as well as “push-out”, the latter referring to a child not able to obtain a place at the next level of education because of lack of places);
- examination scores grade 9;
- enrolment grade 10;
- socioeconomic equity in participation in grade 9 exam among girls,

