### Secondary

1. Both interventions will significantly reduce school dropout, and increase secondary school enrolment, school attendance, exam scores and employment among adolescent girls.
2. Both interventions will significantly reduce early marriage, sexual risk behaviour and increase modern contraceptive use since the economic component will increase girls’ motivation to avoid pregnancy, and the community component will change behavioural and normative beliefs concerning contraceptive use.

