## Outcomes

### *Primary outcomes:*

- incidence of births within 8 months of the end of the intervention period;
- incidence of births before girls’ 18^th^ birthday;
- proportion of girls who sit for grade 9 exam.

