| Proportion of girls who sit for grade 9 exam in control arm | 0.70 |  |
| Effectiveness of combined intervention vs control | +26.5% | i.e. proportion completing in combined intervention arm assumed to be 0.886 |
| Effectiveness (i.e. (1-RR)×100 of economic intervention vs control | +15% | i.e. proportion completing in economic intervention arm assumed to be 0.805 |
| Effectiveness of combined intervention vs economic intervention | +10% | The combined intervention will offer a [1+(0.886/0.805)] , i.e. 10% relative increase compared to the economic intervention alone. |
| Cluster size | 28 | See assumptions for the outcome “incidence of births before girls’ 18th birthday” |
| ICC | 0.02 | We have no information on the ICC for this outcome but have assumed it to be higher than for pregnancy |
| Z_1_ | 1.96 |  |
| Power for comparison of economic intervention vs combined intervention | 95% | We need 29 clusters in each of the intervention arms to have 95% power to detect the assumed difference |
| Power for comparison of economic intervention vs control | 95% | We need 24 clusters in each of the arms to have 95% power to detect the assumed difference |
| Power for comparison of combined intervention vs control | >95% | We need 7 clusters in each arm to have 95% power to detect the assumed difference |

Taking the largest of these sample sizes, we need 63 clusters in each of the intervention arms. Since we expect larger differences between each of the intervention arms and the control arm than between the two intervention arms themselves, we can reduce the total number of clusters by allowing for a lower sample size in the control arm. Thus we will include at least 63 economic intervention clusters, 63 combined intervention clusters and 31 control clusters, i.e. 157 clusters with a total of 31 x 157=4867 or approximately 4900 girls..

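### Two secondary outcomes, grade 9 exam scores and boyfriends among unmarried girls, depend on a status after randomisation that the interventions are meant to change, so arm differences can reflect who is counted

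*Protocol*

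**What the plan says.** The Protocol, Secondary outcomes, lists "examination scores grade 9" under School-related and "proportion of unmarried girls with boyfriend" under Marriage. It gives neither an analysis set for the scores nor a value for a girl who does not sit.

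Sitting is a primary outcome: "proportion of girls who sit for grade 9 exam". The Sample size section plans it at 0.70 in the control arm (row "Proportion of girls who sit for grade 9 exam in control arm"), then "i.e. proportion completing in economic intervention arm assumed to be 0.805" and "i.e. proportion completing in combined intervention arm assumed to be 0.886".

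The secondary hypotheses say that both interventions will reduce school dropout and "increase secondary school enrolment, school attendance, exam scores and employment among adolescent girls". They also say that both will reduce early marriage.

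The Statistical methods section sets intention-to-treat analysis by the allocation of the cluster. Its only exclusion rule nearby removes girls already married at the start of the intervention, and it applies to the ever-married outcome alone.

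**The concern.** Both outcomes are observed, or counted, only in girls with a certain status after randomisation, and the plan expects that status to differ by arm. A comparison within such groups is no longer between groups formed by randomisation.

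For scores, an arm that keeps more girls in school also brings more girls to the exam. If the added girls tend to score lower, the mean among sitters falls although no girl does worse. The combined arm, expected to work best, would be affected most. The trial could then report lower scores against its own hypothesis, because it had succeeded on a primary outcome.

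For boyfriends, a girl whose marriage is averted enters the denominator. If such girls have boyfriends more often than girls who would be unmarried in either arm, the proportion rises although no girl's behaviour got worse.

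**Working it through.** **Planning figures.** Inputs from the Sample size section: cluster size 28, ICC 0.02 for sitting, 95% power, z = 1.96. Design effect = 1 + 27 × 0.02 = 1.54. Clusters per arm = (1.96 + 1.645)² × [p1(1 − p1) + p2(1 − p2)] × 1.54 / (28 × (p1 − p2)²).

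- Economic vs combined: 28.1, rounded up to 29 (Protocol: 29)
- Economic vs control: 23.8, rounded up to 24 (Protocol: 24)
- Combined vs control: 6.4, rounded up to 7 (Protocol: 7)

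So 0.70, 0.805 and 0.886 are the figures the trial was planned on.

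**Share of added sitters**, if the interventions only add sitters:

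- Economic vs control: 1 − 0.70/0.805 = 13.0%
- Combined vs control: 1 − 0.70/0.886 = 21.0%
- Combined vs economic: 1 − 0.805/0.886 = 9.1%

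**Shift in the mean among sitters with no effect on scores.** Assumptions: scores are normal with SD 1; propensity to sit is standard normal with correlation r to the score; a girl sits if her propensity exceeds the cut-off c that gives her arm's rate. The mean among sitters is r × φ(c)/p, where φ(c)/p is 0.497 (control), 0.342 (economic) and 0.218 (combined). The differences for r from 0 to 0.7 are:

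- Economic vs control: −0.154r, i.e. 0 to −0.11 SD
- Combined vs control: −0.279r, i.e. 0 to −0.20 SD
- Combined vs economic: −0.125r, i.e. 0 to −0.09 SD

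**Chance of a significant result in the harmful direction.** The design has 31, 63 and 63 clusters with 28p sitters each: 19.6, 22.5 and 24.8. The score ICC is not in the Protocol, so it is varied. At ICC 0.1, combined vs control: SE² = (1 + 18.6 × 0.1)/607.6 + (1 + 23.8 × 0.1)/1562.9 = 0.00471 + 0.00216, so SE = 0.083. The economic comparison also gives 0.083. The chance is Φ(−1.96 + shift/SE), taking the size of the shift:

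| r | Combined vs control, ICC 0.02 / 0.1 / 0.2 | Economic vs control, ICC 0.02 / 0.1 / 0.2 |
|---|---|---|
| 0 | 2.5% at each | 2.5% at each |
| 0.3 | 32% / 17% / 12% | 12.5% / 8% / 6% |
| 0.5 | 69% / 39% / 26% | 27% / 15% / 11% |
| 0.7 | 93% / 65% / 45% | 47% / 25% / 17% |

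**Width of trimming bounds.** If the interventions only add sitters, trimming the added share from the top or bottom of the arm with more sitters moves its mean by φ(c)/q. Here q is the ratio of the two sitting rates and c the normal cut-off for q. For SD 1 this is ±0.24 (economic vs control), ±0.37 (combined vs control) and ±0.18 SD (combined vs economic).

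**Boyfriend outcome.** Every input here is an assumption: 20% married in control, 25% or 40% of marriages averted, and a boyfriend rate of 25% in girls unmarried in either arm and 50% to 75% in girls whose marriage is averted. Control shows 25.0%.

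- 25% averted: (0.80 × 0.25 + 0.05 × 0.50)/0.85 = 26.5%; with 75%, 27.9%
- 40% averted: (0.80 × 0.25 + 0.08 × 0.50)/0.88 = 27.3%; with 75%, 29.5%

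If both groups have the same boyfriend rate, the shift is zero.

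**The case against.** Four objections have force.

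First, the Protocol nowhere says that scores will be compared among sitters only. The restriction is implicit, and an SAP could assign non-sitters a value or report bounds. That stands as a limit. It does not remove the point: a score has no natural value for a girl who did not sit, the hypothesis of higher scores is in the Protocol itself, and the restriction to unmarried girls is explicit.

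Second, the bias needs the added girls to score lower. The Background mainly describes barriers of cost and of secondary school places, not low ability. At zero correlation there is no bias. The Statistical methods also allow adjustment for imbalanced baseline predictors, which may remove part of it. So the direction is plausible but not established, and no single figure for false harm should be quoted.

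Third, a reader might infer that these outcomes break the intention-to-treat commitment. The documents do not support that. The Protocol defines intention-to-treat by the allocation of the cluster, whether or not the intervention is accepted; it does not fix the denominator of each outcome. The fair criticism is a denominator that may change by arm.

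Fourth, sitting and marriage are reported as outcomes in their own right, so a careful reader could see that the groups differ. That helps interpretation but does not make the conditional comparison valid.

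The boyfriend outcome could also be read as unmarried with a boyfriend, over all girls. That fixes the denominator, but averted marriages still raise the numerator: with 20% married, 40% averted and rates of 25% and 50%, from 20% to 24%.

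**Conclusion.** The point holds as a risk of selection bias in two secondary outcomes. The 13% and 21% shares of added sitters follow from the Protocol's own rates, given that the interventions only add sitters. The score shifts of up to 0.11 and 0.20 SD rest on an assumed correlation. The chance of a significant false harm for combined vs control is 2.5% at zero correlation and 12% to 93% for correlations of 0.3 to 0.7 with a score ICC of 0.02 to 0.2. That spread shows the sitters-only comparison cannot carry the hypothesis of higher exam scores; it does not show that the trial will report harm. The boyfriend shift, about 1.5 to 4.5 percentage points in the illustration, depends wholly on assumed rates. The primary outcomes and the sample size are unaffected.

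**What to change.** **Exam scores.** Do not test the hypothesis of higher scores on sitters alone. Label that comparison conditional on sitting and descriptive, and show trimming (Lee) bounds for girls who would sit under either arm, stating the assumption that the interventions only add sitters. Beside it, report an outcome over all randomised girls, such as having passed the grade 9 exam, with the pass criterion fixed in advance. State that it combines sitting and performance and is not evidence on scores alone.

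Ranking non-sitters lowest should not stand in for a score analysis. In the model above, with no effect on any girl's score, an intervention girl outranks a control girl (ties counted as half) with probability 0.53 to 0.55 (economic) and 0.55 to 0.59 (combined) for correlations of 0.7 down to 0. Sitting alone would then appear to confirm the hypothesis.

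**Boyfriend outcome.** Replace it with relationship status over all girls in three exclusive categories: married or cohabiting, unmarried with a boyfriend, unmarried without. Read the three jointly, because the middle category rises by itself when marriages are averted.

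**Cost.** Changes to outcome wording and reporting, using data the trial already plans to collect. The composite mixes sitting with performance, and the bounds are wide, so the trial may have little to say on scores as such.
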